Exercise training seems to improve sympathetic activity control and/or abnormal cardiovascular responses to muscle metaboreflex activation in several chronic conditions [17–20]. Although very little information is available on the potential mechanisms by which exercise training favors the muscle metaboreflex, they seem to include a wide spectrum of adaptations, as increased muscle perfusion with lower metabolite accumulation, greater antioxidant capacity, and changes in the expression of receptors evoking metaboreflex (i.e., the transient receptor potential vanilloid receptor 1 –TRPv1) [21]. Individuals with impaired metaboreflex have deficiencies in one or more of those mechanisms, and therefore might be more responsive to exercise training than healthy individuals [21]. This is the case of PLHIV, who often present lactic acidosis [22] and attenuated pressor response to metaboreceptor stimulation [23].

Despite this, we could not find research investigating muscle metaboreflex adaptations and its underlying mechanisms to exercise training in PLHIV. This would be nonetheless useful to determine the potential impact of exercise training on mechanisms controlling autonomic modulation during exercise, which have prognostic value [24]. Thus, the aim of the present study is to describe the experimental protocol of a randomized controlled trial designed to investigate the effects of a multimodal supervised exercise program (i.e., aerobic, resistance and flexibility exercises) on hemodynamic and autonomic responses to muscle metaboreflex activation in PLHIV. In addition, potential mechanisms of exercise training adaptations in the muscle metaboreflex will be analyzed by assessing blood lactate concentration and activating TRPv1. We will test the hypothesis that a multimodal exercise training would be able to increase the neurocardiovascular responses during metaboreflex activation by reducing blood lactate levels at rest and increasing TRPv1 sensitivity.

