### Sample size calculation and statistical analysis

Sample size was calculated using GPower 3.1.9.4 (Universität Kiel, Kiel, Germany) to detect longitudinal differences between groups in systolic BP response due to metaboreflex gain. Considering a between-group difference of 3.5 mmHg (standard deviation of 4.6 mmHg) [23], 80% power and 5% significance level, and increasing the sample size by 50% to account for losses to follow up, a total of 21 participants in each group was calculated as necessary.

Descriptive analysis will consist of mean and standard deviation for continuous variables and percentage for categorical variables. Data normality will be checked by the Shapiro Wilk test, and data will be presented as mean and standard deviation or percentage, whenever appropriate. A cross-sectional comparison between PLHIV-T, PLHIV-C and CONT will be performed at baseline by means of one-way ANOVA (continuous) or chi-squared test (categorical).

Longitudinal effects of exercise training on primary and secondary outcomes will be evaluated through linear mixed models (LMM) including treatment (PLHIV-T or PLHIV-C) and time as fixed effects, and group *vs*. time interaction. LMM, which correlates with repeated measures over the time, allows an intention-to-treat analysis as it includes all observations of each one of the participants, regardless of losses to follow-up or noncompliance to exercise protocol. Residual plots of all models will be examined and the likelihood-ratio test will be used to compare and select random intercept or random slope models. Data analysis will be performed using Stata 13.0 (StataCorp, College Station, TX, USA), and in all cases the statistical significance will be set at *P* ≤ 0.05.

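### The stated sample-size inputs do not give 21 per group: read as a two-group comparison they give 67% power with no losses and 49% at 14 completers per arm, not 80%

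*Protocol article*

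**What the plan says.** The section on sample size calculation and statistical analysis says that GPower was used "to detect longitudinal differences between groups in systolic BP response due to metaboreflex gain". The inputs are one difference and one SD, with a power and a significance level: "Considering a between-group difference of 3.5 mmHg (standard deviation of 4.6 mmHg) [23], 80% power and 5% significance level". The size was then adjusted by "increasing the sample size by 50% to account for losses to follow up", and the result is that "a total of 21 participants in each group was calculated as necessary". The section on participants and recruitment agrees: 42 PLHIV are randomized 1:1, 21 to training and 21 to control.

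The planned analysis is a linear mixed model with group, time and their interaction. The text does not give the test family used in the calculation, its sidedness, whether the SD belongs to a single visit or to the change over 12 weeks, or a pre-post correlation.

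The source cited for the difference and SD, reference [23], appears in the Introduction as evidence that PLHIV have an "attenuated pressor response to metaboreceptor stimulation [23]", and the Discussion cites it to the same effect. Both sections also say that the authors found no study of exercise training and the muscle metaboreflex in PLHIV.

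**The concern.** All the numbers needed for a simple two-group calculation stand next to the result, and they do not lead to it. The standardized difference is about 0.76, and 14 completers per arm is too few to detect it with 80% power in an ordinary between-group comparison.

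BP is a primary outcome, and its systolic response during metaboreflex activation is the variable that sizes the trial. If the true power for 3.5 mmHg is well below 80%, a non-significant result says little about whether an effect of that size exists, while the article tells readers that the trial was built to find it.

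**Working it through.** **Inputs** (all from the sample size section unless noted): difference 3.5 mmHg; SD 4.6 mmHg; power 80%; significance level 5%; inflation 50%; 21 per group; 1:1 allocation (participants and recruitment). Sidedness is not stated; two-sided is assumed first, then one-sided.

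**Step 1. The plan's own figure, taken backwards.** 21 / 1.5 = 14 completers per arm. This corresponds to a loss of 7/21 = 33%.

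**Step 2. Size from the stated inputs**, with 4.6 mmHg as the SD of the compared quantity.
- d = 3.5 / 4.6 = 0.761.
- Normal approximation: n per arm = 2 × (1.960 + 0.842)² / 0.761² = 27.1, so 28.
- Exact two-sample t-test: 28 per arm gives 79.8% power and 29 gives 81.3%, so 29.
- After the plan's own 50%: 28 × 1.5 = 42 and 29 × 1.5 = 43.5, so 42 to 44 per arm (84 to 88 PLHIV), against 21 per arm (42 PLHIV) planned.

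The stated figure is not reproduced.

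**Step 3. Power at the planned size** (exact t-test, d = 0.761):

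| Completers per arm | Two-sided 5% | One-sided 5% |
|---|---|---|
| 14 (full loss allowance used) | 49% | 62% |
| 21 (no losses) | 67% | 78% |

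A one-sided test needs 23 per arm, so it also falls short at both sizes.

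**Step 4. What the design can detect** (two-sided, 80% power, SD 4.6). The detectable d is 1.10 at 14 per arm and 0.886 at 21. In mmHg this is 1.10 × 4.6 = 5.1 and 0.886 × 4.6 = 4.1. The 95% CI half-width, t × 4.6 × √(2/n), is 3.6 mmHg at 14 per arm and 2.9 mmHg at 21.

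**Step 5. The other reading of the SD.** If 4.6 mmHg is a single-visit SD and the change is compared, the change SD is 4.6 × √(2(1 − r)), where r is the pre-post correlation. The article gives no r, so it is varied here as an assumption:

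| r | Change SD (mmHg) | Power, 14 per arm | Power, 21 per arm |
|---|---|---|---|
| 0 | 6.51 | 28% | 40% |
| 0.3 | 5.44 | 37% | 53% |
| 0.5 | 4.60 | 49% | 67% |
| 0.7 | 3.56 | 71% | 87% |
| 0.75 | 3.25 | 78% | 93% |

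For 80% power the change SD must be at most 3.5/1.10 = 3.18 mmHg at 14 per arm, or 3.5/0.886 = 3.95 mmHg at 21. Solving r = 1 − SD²/(2 × 4.6²) gives r of about 0.76 and 0.63.

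**The case against.** The strongest reply is that 49% cannot be called the trial's real power. The article speaks of longitudinal differences and plans a repeated-measures model. If 4.6 mmHg is a single-visit SD and the correlation is high, power at r = 0.7 is 71% to 87%, and 80% is within reach. Likewise, 14 completers per arm reflects a loss allowance, not a forecast; 49% is the low end of a range that reaches 67% without losses. Both points stand. A reader might infer that the trial is simply a coin-flip for its target effect; the document does not support that without conditions. What the reply does not supply is the correlation on which it depends: the article states none, so its inputs still do not yield 80%.

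A reader might also want to say how 14 arose. Several routes lead there. One reads the 28 per arm as a total. Another is a within-between interaction with f = d/2 = 0.38 and r of about 0.05 to 0.1, which gives 28 in total. That setting overstates the interaction: a 3.5 mmHg difference in change corresponds to f = d/4 = 0.19, and with r = 0.5 this returns the same 49%. The document does not show which route was taken, so any account is conjecture, and the point does not need one.

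Finally, one might assert that 3.5 mmHg is an HIV-versus-uninfected contrast and not a training effect. The other citations of [23] and the reported absence of training studies make that plausible, but the article does not say which quantity was taken from the source, and the source is not at hand. It supports a request to state the origin, no more.

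**Conclusion.** The point holds in conditional form. The stated inputs do not give 21 per group, and the 80% claim does not follow from them.

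- If 4.6 mmHg is the SD of the compared quantity, which is the plain reading, about twice the implied 14 completers per arm are needed, and the trial has 49% to 67% power two-sided, or 62% to 78% one-sided, depending on losses.
- If it is a single-visit SD, 80% requires an unstated correlation of about 0.63 with no losses or 0.76 with the full allowance used.

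These figures assume equal arms, a common SD and one comparison at the 5% level. On the first reading, a null estimate with 14 per arm would carry a CI half-width of 3.6 mmHg and so could not rule out the 3.5 mmHg target. Because the mismatch lies in the central design claim, it should be corrected.

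**What to change.** Keep 42 PLHIV and replace the 80% statement with what the design delivers. With 4.6 mmHg as the SD of the compared quantity and a two-sided test, that is 67% power for 3.5 mmHg with no losses and 49% with 14 completers per arm; equivalently, 80% power for 4.1 and 5.1 mmHg respectively.

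In the same paragraph, state:
- the test and its sidedness;
- whether 4.6 mmHg is a single-visit or a change SD;
- any pre-post correlation assumed and its basis. If 4.6 mmHg is a single-visit SD, the power should be quoted for that correlation, with a range around it;
- where 3.5 mmHg comes from and which contrast it represents.

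This changes wording only; recruitment, conduct and the planned model are untouched. The cost is that the published power becomes less favourable.

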## Materials and methods

### Study design

This single-center randomized clinical trial will be performed at the Laboratory of Physical Activity and Health Promotion (LABSAU) at the University of Rio de Janeiro State (RJ, Brazil), where a supervised exercise program particularly designed for PLHIV is held since 2005. PLHIV will be recruited in the outpatient clinic of the University hospital, and uninfected volunteers matched for age, sex and body mass will be randomly recruited from the staff of the same institution to compose a reference group. All subjects will receive oral and written instructions about the study risks and benefits and will be included in the study only after giving written informed consent. Recruitment, pre-participation screening and data collection will occur between February 2022 and December 2023. We believe that results will be available for analysis in 2024.

The trial was registered at ClinicalTrials.gov (registration number: NCT04512456, date of registration: August 13, 2020) and approved by the Ethics Committee of the Pedro Ernesto University Hospital (approval number 41955620.2.0000.5259, opinion number 4.520.721, approved in February 2, 2021). The study complies with the SPIRIT 2013 recommendations (Standard Protocol Items: Recommendations for International Trials) (supporting information) [25]. The Fig 1 depicts the overall schedule and time commitment for trial participants [25].

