### Participants and recruitment

Eligible PLHIV will be men and women aged 30- to 50 years, diagnosed with HIV/AIDS [26], but asymptomatic and free from opportunist infections. Exclusion criteria will be: a) use of cART for less than 3 years; b) regular physical exercise (≥ 3 days/week during 30 min) in the last 6 months; c) current or past diagnosis of hypertension, coronary artery disease, ischemic disease, pulmonary disease, diabetes mellitus, Chagas disease, tuberculosis, or heart failure; d) malnutrition; e) use of antidepressant or antihypertensive medication, and f) smoking habit. Uninfected controls will be screened for items b, c, d, e, and f.

Forty-two PLHIV will be randomized through a random code generator software (www.randomization.com) at a ratio of 1:1 into intervention or control groups. Therefore, the experiment will have three groups: a) PLHIV under training (PLHIV-T; n = 21), which will enroll in the multimodal exercise training during 12 weeks; b) PLHIV controls (PLHIV-C; n = 21), which will remain in clinical care and shall not to change their physical activity behavior; c) Uninfected controls (CONT; n = 21), which shall not change their physical activity behavior. For ethical reasons, the PLHIV-C group will have the possibility to undertake the exercise training intervention once the trial ends. Outcomes in PLHIV-T and PLHIV-C will be assessed before randomization at baseline and after intervention, whereas in CONT only at baseline to provide reference values. The study flowchart is presented in Fig 2.

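### The uninfected reference group is matched on age, sex and body mass, but its baseline comparison is a one-way ANOVA without these factors, which can give up precision against an adjusted model

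*Protocol article*

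**What the plan says.** Study design in the protocol article describes the reference group: "uninfected volunteers matched for age, sex and body mass will be randomly recruited from the staff of the same institution to compose a reference group". Participants and recruitment gives its size, "Uninfected controls (CONT; n = 21", against 42 people living with HIV (PLHIV) randomised "at a ratio of 1:1 into intervention or control groups". Outcomes are measured before and after the intervention in the two PLHIV arms, "whereas in CONT only at baseline to provide reference values".

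The section Sample size calculation and statistical analysis names one analysis that uses CONT: "A cross-sectional comparison between PLHIV-T, PLHIV-C and CONT will be performed at baseline by means of one-way ANOVA (continuous" outcomes, with a chi-squared test for categorical ones). No covariate or matching term is given. The mixed model in the same section covers PLHIV-T and PLHIV-C only. The sample size was set "to detect longitudinal differences between groups in systolic BP response due to metaboreflex gain", so no power is claimed for the contrast with CONT.

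**The concern.** The design and the named test do not fit each other. Matching makes the groups alike on age, sex and body mass, so these factors contribute little to the difference between group means. A one-way ANOVA estimates its error from the full spread within groups, including the part due to those factors. Its standard error then overstates the real uncertainty of the CONT contrast, intervals are too wide, and the test rejects less often than its nominal 5% when there is no difference.

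At stake is the precision of the HIV-versus-uninfected comparison at baseline. CONT has no follow-up, so this is the only stated analysis in which those 21 people appear. Because the protocol names the test outright, the point concerns a stated method and not a detail left to another document.

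**Working it through.** **The plan's own figure.** The only stated figure is 21 per group, and it belongs to the longitudinal comparison. The two-sided two-sample normal formula, 2 x (1.96 + 0.84)^2 x (4.6/3.5)^2, gives 28 per group before the 50% increase, so 21 per group is not reproduced that way. That is a separate matter. There is no stated figure for the CONT contrast to reproduce.

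**Inputs.**
- Group sizes: 21, 21 and 21 (Participants and recruitment).
- Difference and SD: "Considering a between-group difference of 3.5 mmHg (standard deviation of 4.6 mmHg". Both are borrowed from the longitudinal calculation.
- Test level: two-sided 5% (the protocol gives 5% and does not state the sides).
- R2, the share of outcome variance explained by age, sex and body mass: not in the documents, so assumed over a range.

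**Step 1: ANOVA standard error, 42 PLHIV v 21 CONT.** 4.6 x sqrt(1/42 + 1/21) = 1.229 mmHg.

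**Step 2: adjusted standard error.** 1.229 x sqrt(1 - R2), if the groups are balanced on the matching factors. At R2 = 0.2 this is 1.229 x sqrt(0.8) = 1.100, so the ANOVA value is too large by 1/sqrt(0.8) = 1.118, or 11.8%.

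**Step 3: power at 3.5 mmHg.** The 42 v 21 column follows from these standard errors with 60 (unadjusted) and 57 (adjusted) degrees of freedom. The three-group column is from simulation, with the PLHIV arms randomised independently and CONT matched to 21 of the 42 PLHIV.

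| R2 | Adjusted SE | ANOVA SE / adjusted SE | Power 42 v 21, unadjusted v adjusted | Power three groups, unadjusted v adjusted |
|---|---|---|---|---|
| 0 | 1.229 | 1.000 | 80% v 80% | 70% v about 69% |
| 0.1 | 1.166 | 1.054 | 81% v 84% | 70% v 74% |
| 0.2 | 1.100 | 1.118 | 83% v 88% | 72% v 80% |
| 0.3 | 1.029 | 1.195 | 84% v 92% | 72% v 85% |

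If CONT is matched to only 21 of the 42, balance with the pooled PLHIV group is not exact. The 42 v 21 figures are then about 81% v 84% at R2 = 0.1 and 82% v 88% at R2 = 0.2, within a point of the table.

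**Step 4: false-positive rate.** In the same simulation the three-group ANOVA rejects a true null about 4.2% of the time at R2 = 0.1 and 3.9% at R2 = 0.2. For the single 42 v 21 contrast under exact balance, a normal approximation gives 3.5% and 2.5%; that approximation reads 4.6% at R2 = 0, so it runs slightly low.

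**Reading the table.** Down the rows, the power of the unadjusted test does not fall; it rises slightly as R2 grows. What is given up is the distance to the adjusted test.

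**The case against.** The strongest reply is that the loss is hypothetical. No passage says how well age, sex and body mass predict any outcome. Ages run only from 30 to 50 years; hypertension, diabetes, heart disease and smoking are excluded; and the responses to mental stress and circulatory arrest are analysed as changes from rest. A low R2 is plausible, and at R2 = 0.05 the 42 v 21 power is 81% v 82%. This stands, and it is why the size can only be given as a range.

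The stakes are also limited. CONT supplies reference values, the trial is not sized for this contrast, the impairment in PLHIV is taken from earlier research, and the stated hypothesis concerns training. This stands too.

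Stronger readings are tempting but not supported:
- A reader might infer that matching lowers the power of the ANOVA. It does not.
- A reader might infer a false-positive rate far below 1%. Simulating 21 matched triplets (one PLHIV-T, one PLHIV-C, one CONT) at a within-set correlation of 0.5 gives 0.4%. However, the protocol randomises 42 PLHIV with a random code generator and describes no matching between arms. With the arms independent, the three-group rate at R2 = 0.5 is about 3.4%.
- A reader might call for a paired or blocked analysis. No pairs or sets are described, and 21 controls cannot form 1:1 pairs with all 42 PLHIV, so matching at group level fits the text as well.

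One could add that covariate lists are usually left to an analysis plan. Here, however, the protocol commits to a specific unadjusted test.

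**Conclusion.** The point holds as a minor one. The reference group is built by matching, and the only stated analysis that uses it ignores the matching factors. If those factors predict the outcome, the standard error of the contrast with CONT is too wide and the test is conservative. For R2 of 0.1 to 0.2, the power given up against an adjusted model is about 4 to 8 points in the three-group test and 3 to 6 points for 42 v 21. At R2 = 0 nothing is given up.

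These figures rest on an assumed R2, on 3.5 and 4.6 mmHg carried over from another comparison, on the same deficit in both PLHIV arms, and on matching that achieves good balance. They also take the baseline comparison to cover outcomes such as blood pressure, since the sentence does not list its variables.

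A reader might infer that the trial's main result is at risk. It is not: the error is in the conservative direction, and the mixed model comparing PLHIV-T with PLHIV-C does not use CONT.

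**What to change.** In Sample size calculation and statistical analysis, replace the one-way ANOVA for continuous outcomes with a linear model of the baseline outcome on group, adjusted for age, sex and body mass. Report the adjusted CONT-minus-PLHIV difference with its 95% CI. Body mass and BMI, which are themselves listed among the anthropometric outcomes, should not be adjusted for body mass. A term for matched set is appropriate only if controls are in fact matched individually, which the protocol would then need to say.

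The cost is one sentence. Age and sex are known from screening, and body mass is already measured under Anthropometry. The model spends three of 60 degrees of freedom, about 1 power point if the factors turn out to be unrelated to the outcome. Recruitment, assessments and the randomised analysis do not change.

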**Fig 3 pone.0265516.g003:**
[figure not shown]
Experimental design.

After a general medical examination and anthropometric measurements, participants will remain 30 min at rest in a supine position before performing a mental stress task and handgrip strength test. The mental stress task will provide information about the integrity of pathways of stress-induced sympathetic responses mediated by the central command. Maximal voluntary contraction (MVC) assessed by the handgrip test will be used to determine the loads applied during the metaboreflex activation protocol, and to detect possible strength differences between groups at baseline and after intervention. Subsequently, the muscle metaboreflex will be activated using a post-exercise circulatory arrest (PECA) protocol, during which blood lactate will be assessed. Then, a capsaicin-based analgesic balm (0.1%, FarmaSite, Itaúna, Brazil) will be applied over the exercising arm to stimulate the metabolically sensitive muscle afferents via TRPv1 receptors [27], and after 30 min of topical application, PECA will be repeated.

Primary outcomes will be BP and heart rate variability (HRV) indices reflecting autonomic modulation. Secondary outcomes will be the heart rate (HR), peripheral vascular resistance (PVR), stroke volume (SV), cardiac output (CO), blood lactate concentration, anthropometric markers, and handgrip MVC.

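### The three-group baseline ANOVA tests a chance difference between two randomised halves of one population and loses power for the one meaningful contrast, PLHIV versus uninfected (minor)

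*Protocol article*

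**What the plan says.** The statistical section of the protocol article (Sample size calculation and statistical analysis) fixes the baseline analysis in one sentence: "A cross-sectional comparison between PLHIV-T, PLHIV-C and CONT will be performed at baseline by means of one-way ANOVA (continuous" variables; categorical variables get a chi-squared test). The threshold is P ≤ 0.05 throughout, and no contrast of all PLHIV against CONT is named.

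Participants and recruitment describes the groups. PLHIV are randomised "at a ratio of 1:1 into intervention or control groups", 21 to each. On timing: "Outcomes in PLHIV-T and PLHIV-C will be assessed before randomization at baseline and after intervention". The third group is not randomised: "Uninfected controls (CONT; n = 21), which shall not change their physical activity behavior". Its role is limited: outcomes are taken in the PLHIV arms twice, "whereas in CONT only at baseline to provide reference values". Study design calls its members "uninfected volunteers matched for age, sex and body mass".

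Experimental design gives handgrip strength a further purpose besides setting the load: "to detect possible strength differences between groups at baseline and after intervention".

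The only effect size in the article belongs to the sample size for the longitudinal comparison: "Considering a between-group difference of 3.5 mmHg (standard deviation of 4.6 mmHg"). No power is stated for the baseline comparison.

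**The concern.** A one-way ANOVA on three groups asks whether any of the three means differ. Two of the groups here cannot differ at baseline except by the luck of the draw. The test therefore mixes a real question (do PLHIV differ from uninfected people?) with an empty one (do two random halves of the PLHIV sample differ?).

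Two things follow. First, a significant difference between PLHIV-T and PLHIV-C would be a false positive, and a non-significant one would not show that the arms are balanced. Second, the real question is tested less sensitively than the same data allow. What is at stake is the baseline reference comparison, which is the only use the article makes of the 21 uninfected volunteers.

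**Working it through.** **Is the arm comparison informative?** PLHIV are measured, then split 1:1 by a random code. Before the split they are one sample from one population, so the expected baseline means of PLHIV-T and PLHIV-C are equal for every variable. With sound randomisation, a test of that equality at P ≤ 0.05 rejects about 5% of the time, always wrongly. This covers the arm-versus-arm part of the baseline handgrip comparison as well. It does not cover the handgrip comparison after the intervention, nor the baseline comparison of PLHIV with CONT; both are real questions.

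**How much power does the three-group test lose?** The plan states no power for this comparison, so there is no figure of its own to reproduce. Inputs:

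- Group sizes 21, 21 and 21 (Participants and recruitment). The 50% allowance in the sample size is for losses to follow-up, so it does not reduce the baseline numbers.
- Equal true means in the two PLHIV arms, from the argument above.
- Two-sided 5% level. The article does not state sidedness, so this is an assumption.
- Standardised PLHIV-versus-CONT difference d. The article gives none. I use 3.5/4.6 = 0.761 as an illustration and show a range.

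Three-group F test, with means (d, d, 0) and SD 1. The grand mean is 2d/3, so

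λ = 21 × [(d/3)² + (d/3)² + (2d/3)²] = 21 × (6/9) d² = 14 d², on 2 and 60 degrees of freedom.

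Pooled contrast, 42 versus 21:

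δ = d / √(1/42 + 1/21) = d / √(1/14), so δ² = 14 d², on 1 numerator degree of freedom.

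The two tests have the same noncentrality. The F test spreads it over two degrees of freedom, one of which belongs to the PLHIV-T versus PLHIV-C difference, where there is nothing to find. At d = 0.761, λ = 14 × 0.761² = 8.10. Power from the noncentral F and noncentral t distributions:

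| d | λ = 14 d² | Three-group F test | 42 versus 21 | Difference (points) |
|---|---|---|---|---|
| 0.5 | 3.50 | 35.3% | 45.3% | 10.0 |
| 0.65 | 5.92 | 55.5% | 66.8% | 11.3 |
| 0.761 | 8.10 | 70.0% | 80.0% | 10.0 |
| 0.9 | 11.34 | 84.5% | 91.2% | 6.7 |

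The smallest difference detectable with 80% power is d = 0.851 for the F test and 0.761 for the pooled contrast. At an SD of 4.6 mmHg these are 0.851 × 4.6 = 3.9 mmHg and 0.761 × 4.6 = 3.5 mmHg. At d = 0.761 the F test needs 26 per group for 80% power; the pooled contrast reaches it with the planned 21.

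Run as a planned contrast inside the three-group ANOVA (60 error degrees of freedom), the pooled comparison again gives 80.0%. The loss therefore comes from relying on the overall F test, not from fitting three groups.

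**The case against.** The strongest reply is that this comparison carries little weight. The stated aim and hypothesis concern the effect of training. That effect is tested by a mixed model on the two PLHIV arms, which makes no use of the baseline ANOVA, and no rule lets a baseline P value choose covariates or change the model. All of this stands, and it is why the point is minor. A reader might infer that the trial could fail to show the impairment it is built on. The article does not support that: impaired metaboreflex is a premise taken from cited work, and the uninfected group only supplies reference values.

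A reader might also infer that dividing baseline data by a later randomisation is itself an error. It is not. Measuring before randomisation is sound, and labelling the data by arm at analysis is routine. The timing shows only that differences between the arms must be chance.

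The effect size is open to challenge too. The 3.5/4.6 figure was set for a longitudinal difference, and whether it suits the contrast with uninfected people depends on a cited study not available here. Hence the range. Power for pairwise 21-versus-21 follow-up tests, with or without a multiplicity correction, would look worse still, but the article states no such tests, so those figures are not part of the case. It could be said that a planned contrast was simply left to a fuller document. The stated analysis, however, is the three-group test, and it is that test which is poorly chosen.

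Finally, the protocol expressly wants to look for baseline strength differences between groups. That purpose is legitimate for PLHIV against CONT, but not as a significance test between the randomised arms.

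**Conclusion.** The point holds as a minor one, confined to the baseline reference comparison. Testing PLHIV-T against PLHIV-C at baseline is uninformative. The three-group F test also gives up about 7 to 11 percentage points of power for PLHIV versus uninfected over d = 0.5 to 0.9 (70% against 80% at d = 0.76). The first conclusion rests only on the randomisation being sound. The second assumes a two-sided 5% level, equal true PLHIV means at baseline, full baseline data on 42 and 21 people, and an illustrative effect size. The direction of the loss is the same at every effect size examined. The inference on the training effect is unaffected.

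**What to change.** Replace the baseline sentence in the statistical section with two statements.

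1. All 42 PLHIV will be compared with the 21 uninfected participants at baseline by one pre-specified contrast, either a planned contrast within the ANOVA or a linear model. It will be adjusted for the matching factors age, sex and body mass, except where the variable compared is itself one of these or an anthropometric marker, since adjustment there would be circular. Categorical variables will be compared between the same two groups.
2. PLHIV-T and PLHIV-C will be described side by side at baseline without P values.

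The handgrip sentence in Experimental design should be brought into line, so that baseline strength is tested only between PLHIV and CONT. The article does not say whether matching is individual or by group; the adjusted model should follow whichever was used. The cost is a change of wording, with no added participants, visits or measurements.
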